## **4.2 Per protocol population**

The per protocol population (PP) includes all patients of the ITT population which were treated following the specifications of the study protocol without major protocol deviations. Excluded from the per protocol population will be patients that meet at least one of the following criteria:

- Violation of one of the following exclusion criteria: exclusive breastfeeding, hospitalisation for serious complicated illness (e.g. chronic illness).
- Not treated according to the allocated intervention group
  - For the RUTF group (for each 14-day supplementation period)
    - less than 12 days of supplement taken by the child
    - less than 12 sachets consumed by the child
    - less than 12 empty sachet counted
  - For the MNP group (for each 14-day supplementation period)
    - less than 24 days of supplement taken by the child
    - less than 24 sachets consumed by the child
    - less than 24 empty sachet counted
  - For all three groups (RUTF, MNP, control): having taken RUTF or MNP outside the study allocation (e.g. as part of measles treatment)
- Patient misses 3 or more scheduled visits
- Patient misses 2 or more consecutive scheduled visits
- Patient misses the last scheduled visit (6 months visit)
- Participation in other feeding programmes

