## **2 Study design**

This is a partially blinded randomized controlled trial with three study groups. Children 6 to 59 months of age presenting at the OPD in Goronyo and diagnosed with one or more of the three study diseases (malaria, diarrhoea and LRTI) are eligible for the study.

Children participating in this study will be randomised to one of 3 study groups to:

- A) Receive 14 days of RUTF supplementation with standard care and treatment or
- B) Receive 14 days MNP supplementation with standard care and treatment or
- C) Be included in a control group receiving standard care and treatment but not receiving nutritional supplementation (control group)

Individual follow-up will be 6 months. During this time, children in the RUTF or MNP group will receive 14 days nutritional supplement every time diagnosed with at least one of the three study diseases, not exceeding more than 14 days supplementation in any 28 day period.

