#### **3.2 Secondary endpoints**

Secondary endpoints include

- Number of NNO’s per study group in a period of 6 months
- Time to NNO
- Number of new events of a study disease in 6 months
- Weight change at 14 days and 28 days after study inclusion, and at end of study period
- Rate of weight change (grams/kg/day) at 14 days and 28 days after study inclusion, and at end of study period
- Proportion of children not gaining weight (including losing weight), measured at day-14 and day-28 after study inclusion.
- Proportion of children developing bilateral oedema, overall and per month
- Proportion of moderate acutely malnourished children improving to a non acutely malnourished state, overall and per month
- Mortality: overall mortality
- Morbidity, including the three study diseases (proportion of children with newly diagnosed diseases), overall and per month
- Proportion of children with a reported cough at clinical visit, overall and per month
- Proportion appetite categories
- Proportion and time pattern of children who were breast-fed at baseline and stopped being breast-fed during the study

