### 5.3 Primary analysis of primary endpoint

The primary endpoint is “negative nutritional outcome” of a child within the 6 months follow-up period. The incidence rate (in formulae below referred to simply as ‘rate’) of “negative nutritional outcome” will be computed as the number of events divided by total observed person-time in each treatment group. As an “event” the first time a child reaches a negative nutritional outcome will be used. The primary analysis of the primary endpoint will be performed on the intention to treat population with no imputation of missing data.

In the primary analysis, RUTF will be compared to the control group

The hypotheses in this step are

$$H_0: \text{rate}_{\text{RUTF}} = \text{rate}_{\text{Control}}$$

vs.

$$H_1: \text{rate}_{\text{RUTF}} \neq \text{rate}_{\text{Control}}$$

where  $\text{rate}_{\text{RUTF}}$  = rate of “negative nutritional outcome” in the children in the RUTF group, and  $\text{rate}_{\text{Control}}$  = rate of “negative nutritional outcome” in the children in the control group.

The comparison of rates among the two treatment groups (RUTF vs. control) will be performed by a Poisson regression model, adjusted for nutritional status at enrolment (fixed effect) and will be performed within one model including the three intervention groups with contrasts for each two-group comparison. The result will be presented as rates for each intervention group, and a rate ratio for the pair-wise comparison (each with 95% confidence intervals). Tests will be two-sided with a significance level of 0.05.

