#### 5.4.5 Per protocol analysis

The analysis as described in 5.4.1 will be repeated for the per protocol population.

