## **5.5 Analysis of secondary endpoints**

All secondary endpoints (as defined in section 3.2) will be compared between the three treatment groups as described in 5.4.1 (p-values will be considered explorative) for the ITT and the PP populations. In addition to the Poisson regression model, logistic regression model, analysis of variance (ANOVA), analysis of covariance (ANCOVA), Cox proportional hazard model, and non-parametric analysis of variance will be used, according to the type of endpoint. In case of relevant differences in baseline characteristics additional adjustment(s) for these factors may be performed. Stratified analyses are planned for secondary endpoints regarding weight and weight change with respect to age, gender, and breast feeding.

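### The any-short-course rule in SAP 4.2 tends to filter RUTF children, but not controls, on later illness, and 5.5 then compares illness in that per-protocol set

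*SAP*

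**What the plan says.** SAP 4.2 defines the per-protocol set by exclusion: "Excluded from the per protocol population will be patients that meet at least one of the following criteria". One block of criteria concerns treatment as allocated. Its RUTF part is headed "For the RUTF group (for each 14-day supplementation period" and sets minimums of 12 days, 12 sachets consumed and 12 empty sachets counted. The only criterion in that block that reaches control is taking RUTF or MNP outside the study allocation. The remaining criteria (eligibility violations, missed visits, other feeding programmes) apply to every arm and do not count courses.

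Section 2 says that supplemented children receive a 14-day course "every time diagnosed with at least one of the three study diseases, not exceeding more than 14 days supplementation in any 28 day period".

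Section 3.2 lists two endpoints that measure study-disease illness: "Number of new events of a study disease in 6 months" and "Morbidity, including the three study diseases (proportion of children with newly diagnosed diseases), overall and per month". Section 5.5 compares all secondary endpoints between groups, with "p-values will be considered explorative) for the ITT and the PP populations".

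For the primary endpoint, 5.3 states: "The primary analysis of the primary endpoint will be performed on the intention to treat population with no imputation of missing data". Section 5.4.5 adds: "The analysis as described in 5.4.1 will be repeated for the per protocol population".

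**The concern.** Taken together, 4.2 and section 2 make each illness that triggers a course one more occasion on which a RUTF child can fail the per-protocol definition. A control child with the same illness history faces no such occasion. Membership of the set therefore depends, in one arm only, on the quantity that 5.5 goes on to compare. This is more specific than the usual reservation about per-protocol sets, because the selection acts on the outcome itself.

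At stake is the reading of a per-protocol morbidity result. If often-ill RUTF children are thinned out and often-ill controls are not, the remaining RUTF group looks healthier even if the supplement does nothing. Reducing the incidence of the three study diseases is part of the aim in section 1, so such a result could be cited in support.

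**Working it through.** The SAP states no figure on this point to reproduce, and gives no illness rate, adherence rate or within-child correlation. All three are assumptions below and are shown as ranges.

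**Inputs from the SAP.** Any one criterion excludes and the RUTF minimums apply per course (4.2). Each diagnosis brings a course, with at most 14 days in any 28, over 6 months (section 2). With course starts at least 28 days apart over 182 days (days 1, 29, 57, 85, 113, 141, 169), a child can have at most 7 courses.

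**Assumptions.** Per-course adherence q is 0.80, 0.90 or 0.95. Within-child correlation ρ is 0, 0.2, 0.5 or 0.8. Illness runs at 0.2, 0.5 or 1.0 diagnoses per child-month, either common to all children or gamma-varying with variance 0.5. There is no true effect, and control is left unfiltered.

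**Step 1: retention by number of courses k.**

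Independent courses: retention = q^k. At q = 0.90, 0.90^1 = 0.900, 0.90^4 = 0.656 and 0.90^7 = 0.478.

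Correlated courses (beta-binomial): a = q(1−ρ)/ρ, b = (1−q)(1−ρ)/ρ, and retention is the product over i = 0 to k−1 of (a+i)/(a+b+i).

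- ρ = 0.5: a = 0.9, b = 0.1. Four courses: 0.9 × 0.95 × 0.9667 × 0.975 = 0.806. Seven courses: 0.765.
- ρ = 0.8: a = 0.225, b = 0.025. Four courses: 0.9 × 0.98 × 0.9889 × 0.9923 = 0.865. Seven courses: 0.853.

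Retention falls with k in each case, but much less steeply when adherence clusters within the child.

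**Step 2: effect on the illness rate ratio.** Without the 28-day cap, with independent courses and a Poisson illness count of mean m, weighting each child by q^(1+k), where k is now the number of repeat courses, gives a retained mean of mq. The null ratio is then q. The cap weakens the link, so the capped case was simulated (300,000 children per setting; Monte Carlo standard error at most 0.0021). Per-protocol rate ratio, RUTF/control, true value 1.00, as the range over the illness-rate assumptions:

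| q | ρ = 0 | ρ = 0.2 | ρ = 0.5 | ρ = 0.8 |
|---|---|---|---|---|
| 0.95 | 0.95–0.99 | 0.97–0.99 | 0.98–1.00 | 0.99–1.00 |
| 0.90 | 0.91–0.97 | 0.94–0.99 | 0.96–0.99 | 0.99–1.00 |
| 0.80 | 0.81–0.94 | 0.87–0.97 | 0.93–0.99 | 0.97–1.00 |

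A separate simulation with independent courses and a mean of 1, 2 or 4 repeat illnesses in 6 months gave similar values: at q = 0.90, 0.93–0.96 (Poisson) or 0.91 (gamma); at q = 0.80, 0.86–0.92 or 0.81–0.82.

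At q = 0.90 the proportion with any new diagnosis falls by 0.1 to 3.4 percentage points if courses are independent, and by 0.0 to 1.5 points at ρ = 0.5.

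**Step 3: what would cancel it.** This is the per-course adherence that an often-ill child needs to match the 90% retention of a one-course child:

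| ρ | 4 courses | 7 courses |
|---|---|---|
| 0 | 0.90^(1/4) = 97.4% | 0.90^(1/7) = 98.5% |
| 0.5 | 95.0% | 96.0% |
| 0.8 | 92.6% | 93.3% |

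As ρ approaches 1, no rise above 90% is needed.

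**The case against.** The strongest reply has four parts.

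- **Adherence may be a trait of the household.** The same caregiver normally gives every course, so independence is the least plausible setting. This stands. At ρ = 0.8 the distortion is close to nil. A reader might infer from the independent-course break-evens that only a marked rise in adherence among often-ill children could cancel the effect. That does not follow: stable adherence removes it with no rise at all.
- **Control is filtered too.** Supplement taken outside the allocation, other feeding programmes and missed visits remove children in every arm, and some of these may track illness. This also stands. The calculation leaves control unfiltered, so it isolates the per-course rule and does not predict the net ratio. The SAP does not allow one to say whether the other criteria add to the shift or offset it.
- **The any-course reading is an inference.** The per-course phrase could be taken only to fix the unit of the minimum. That is possible, but 4.2 offers no other way of combining courses, and one failing course is the natural reading beside an exclusion on any one criterion.
- **The consequence is small.** The intention-to-treat morbidity result will be reported alongside, and the p-values are explorative. This is why the point is minor. It does not dispose of it, because an explorative label deals with multiplicity and not with bias in the estimate.

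**Conclusion.** The point holds as a minor one. On the natural reading of 4.2, and unless adherence is essentially fixed within a child or rises with repeat illness, RUTF retention in the per-protocol set falls with illness count while control has no matching rule. The per-course rule alone then tends to push the null illness rate ratio below 1. At 90% adherence the shift is up to about 9% if courses are independent, 1% to 4% at correlation 0.5, and at most about 1% at 0.8. These sizes rest wholly on assumed inputs, and the net ratio is less certain still because of the exclusions that also act in control.

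Two stronger readings are not supported. The primary result is not put in doubt: its analysis is intention to treat and this rule does not touch it. Nor is the per-protocol repeat of the primary endpoint in 5.4.5 shown to be biased. That would require illness to raise the risk of a negative nutritional outcome, which is possible but is not quantified here.

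MNP has the same per-course structure but is left out of the figures, because its 24-day minimum cannot be met within a 14-day course as written.

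**What to change.** In 5.5, state that "Number of new events of a study disease in 6 months" and the proportion of children with newly diagnosed study diseases will be analysed in the intention-to-treat population only. All other secondary endpoints can stay in both populations.

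The cost is one sentence and the loss of a per-protocol result for these two endpoints. No data, visits or sample size change. Judging adherence on the enrolment course alone would make retention independent of later courses under the same model, but it would keep children who did not take their repeat courses. It is not a good substitute for the main per-protocol set and is not needed once the two endpoints are restricted.

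### The MNP per-protocol rule requires 24 days of supplement in a 14-day period, so no supplemented MNP child can stay in the per-protocol set

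*SAP*

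**What the plan says.** Section 4.2 of the SAP builds the per-protocol population by exclusion: "Excluded from the per protocol population will be patients that meet at least one of the following criteria". One of those criteria is not having been treated as allocated, and it is spelled out separately for each supplement.

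- **RUTF group**, per 14-day period: "less than 12 days of supplement taken by the child", with the same figure of 12 for sachets consumed and for empty sachets counted.
- **MNP group**, introduced by "For the MNP group (for each 14-day supplementation period"): "less than 24 days of supplement taken by the child", then "less than 24 sachets consumed by the child" and "less than 24 empty sachet counted".

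Section 2 sets each course at 14 days and limits repeat courses: "not exceeding more than 14 days supplementation in any 28 day period". On the use of the population, section 5.4.5 states: "The analysis as described in 5.4.1 will be repeated for the per protocol population". Section 5.5 adds that all secondary endpoints are analysed in both populations.

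**The concern.** The MNP day criterion asks for more days than the period contains. All three MNP lines carry the figure 24, just as all three RUTF lines carry 12. This suggests that a sachet number was copied into the day line.

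At stake is whether the per-protocol analysis can be run for the MNP arm at all. The comparison that suffers most is the third step of the hierarchy, RUTF versus MNP for non-inferiority. Non-adherence tends to pull arms together and so favours a non-inferiority conclusion in the intention-to-treat population. By general convention the per-protocol set is the cross-check for that, although the SAP does not itself give it this role.

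There is a second risk. A programmer who meets the impossible rule must either produce an empty arm or choose another threshold. If that choice is made with outcome data at hand, who counts as adherent is no longer prespecified.

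**Working it through.** **Inputs**

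| Quantity | Value | SAP section |
|---|---|---|
| Length of one supplementation period | 14 days | 2, 4.2 |
| Cap on supplementation | 14 days in any 28 | 2 |
| MNP minimum days per period | 24 | 4.2 |
| MNP minimum sachets, consumed and empty | 24 each | 4.2 |
| RUTF minimum days per period | 12 | 4.2 |
| How criteria combine | any one excludes | 4.2 |
| Entry to the intention-to-treat population | at least one dose | 4.1 |

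**Step 1. Share of days required.** Share = minimum days / days available.

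- RUTF: 12/14 = 85.7%.
- MNP: 24/14 = 171.4%.

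**Step 2. Day counts that pass.** A child can have 0 to 14 days of supplement in a period.

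- RUTF, at least 12 days: 12, 13 and 14 pass.
- MNP, at least 24 days: none passes, since the maximum of 14 is below 24.

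**Step 3. Does the wording about each period help?** No. Every MNP period fails the day line, so the result is the same whether one failed period excludes a child or all periods must fail. Nor can 24 be a total over several courses, because the rule is stated per period.

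**Step 4. A fully adherent MNP child.** The SAP gives no daily sachet number, so 1, 2 and 3 a day are assumed in turn. Such a child has 14 days of supplement and 14 times the daily number of sachets.

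| Sachets per day (assumed) | Sachets in 14 days | 24 as a share | Excluded if any one line fails | Excluded only if all three fail |
|---|---|---|---|---|
| 1 | 14 | 171.4% | yes | yes |
| 2 | 28 | 85.7% | yes | no |
| 3 | 42 | 57.1% | yes | no |

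Under the any-one rule, perfect adherence leads to exclusion in every row. At 2 sachets a day, 24 of 28 is 85.7%, exactly the RUTF share. This supports the view that 24 was meant as a sachet count.

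**Step 5. What is left.** The per-protocol population is a subset of the intention-to-treat population, which requires at least one dose. Every MNP child who could enter has therefore started a course, and every course fails. The number of MNP children remaining is 0.

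**Step 6. Analyses affected.**

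- RUTF versus control, per protocol: can be run.
- MNP versus control, per protocol: cannot be run.
- RUTF versus MNP non-inferiority, per protocol: cannot be run.
- Secondary endpoints, per protocol, any comparison with MNP: cannot be run.

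**The case against.** Four points can be made in the plan's defence.

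1. **The main result is untouched.** The primary analysis is RUTF versus control in the intention-to-treat population, which is also the comparison the trial is powered for. The per-protocol analysis is a repeat under secondary analyses, and the p-values for secondary endpoints are exploratory. Step iii is confirmatory only if steps i and ii are both significant. All of this is correct and limits the damage.
2. **The slip would be noticed.** An empty arm would show in the first per-protocol table and raise a query, so silent bias is unlikely. This is fair, but the threshold would then be settled late, perhaps with outcomes known.
3. **The list could be read differently.** The any-one wording governs the top-level criteria, while the three MNP lines are nested under one of them with no conjunction. If all three had to fail together, a fully adherent child would stay in at 2 or 3 sachets a day. This is the less natural reading, and the day line would still be wrong: it would always be failed and so would do no work.
4. **The sachet lines are not shown to be wrong.** This is accepted. Whether 24 sachets is sensible depends on the number dispensed per course, which this SAP does not state.

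**Conclusion.** The concern holds. The MNP day criterion cannot be met: 14 days are available and 24 are required. That conclusion needs only the period length and the threshold, both stated in the SAP.

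The further conclusion, that the per-protocol MNP group is empty, rests on reading the three lines as separate grounds for exclusion, as the section's opening sentence indicates. On that reading 100% of MNP courses fail, and two of the three section 5.4.1 comparisons are lost per protocol, together with the per-protocol MNP comparisons on secondary endpoints.

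The origin of the 24 as a sachet count is an inference and is not needed for the conclusion. Although the harm is confined to per-protocol comparisons involving MNP, the correction is a must-fix because the rule cannot be executed as written.

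**What to change.** In section 4.2, replace the MNP day criterion with one that can be met within 14 days. Using the RUTF group's threshold, fewer than 12 of 14 days, would judge both supplemented arms alike. This is a suggestion from the parallel structure of the two lists, since the SAP does not state the intended figure.

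In the same edit, state explicitly that failing any one of the three lines excludes a child. As a consistency check only, compare the two 24-sachet lines with the number of sachets the protocol dispenses per course.

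The cost is a one-line SAP correction, with no change to data collection, sample size or the primary analysis. It should be dated and approved before outcomes are compared by group, so that per-protocol membership is fixed in advance.

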## **4.3 Completed the study**

Patients will be considered as having 'completed the study' if they have attended at least the first and last scheduled visit at 6 months.

## **4.4 Baseline drop-out**

All patients enrolled who dropped out before the start of randomized treatment.

# **5 Statistical analysis**

## **5.1 Analysis of baseline data**

All available data at baseline will be analysed descriptively for each intervention group and in total. Results will be summarised as frequencies and percentages for nominal data; as means, standard deviations, and range for continuous data; and as medians, quartiles, and ranges for ordinal data.

Differences regarding baseline variables will be checked for clinical relevance between the three treatment groups.

The flow of participants will be described (e.g. number screened, recruited, randomized, emergency unblinding, etc.). Number and reasons for drop-out, lost-to-follow-up, or withdrawal will be presented. If possible respondents and non-respondent will be compared.

## **5.2 Compliance**

Compliance to RUTF and MNP will be assessed through questionnaire and collection of returned supplement sachets.

Compliance is measured as the percentage of dispensed sachets returned empty and will be described by mean percentage (with range and standard deviation) for each treatment group.

### 5.3 Primary analysis of primary endpoint

The primary endpoint is “negative nutritional outcome” of a child within the 6 months follow-up period. The incidence rate (in formulae below referred to simply as ‘rate’) of “negative nutritional outcome” will be computed as the number of events divided by total observed person-time in each treatment group. As an “event” the first time a child reaches a negative nutritional outcome will be used. The primary analysis of the primary endpoint will be performed on the intention to treat population with no imputation of missing data.

In the primary analysis, RUTF will be compared to the control group

The hypotheses in this step are

$$H_0: \text{rate}_{\text{RUTF}} = \text{rate}_{\text{Control}}$$

vs.

$$H_1: \text{rate}_{\text{RUTF}} \neq \text{rate}_{\text{Control}}$$

where  $\text{rate}_{\text{RUTF}}$  = rate of “negative nutritional outcome” in the children in the RUTF group, and  $\text{rate}_{\text{Control}}$  = rate of “negative nutritional outcome” in the children in the control group.

The comparison of rates among the two treatment groups (RUTF vs. control) will be performed by a Poisson regression model, adjusted for nutritional status at enrolment (fixed effect) and will be performed within one model including the three intervention groups with contrasts for each two-group comparison. The result will be presented as rates for each intervention group, and a rate ratio for the pair-wise comparison (each with 95% confidence intervals). Tests will be two-sided with a significance level of 0.05.

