### **3 Endpoints**

#### **3.1 Primary endpoint**

The primary endpoint is “negative nutritional outcome (NNO)” of a child within the 6 months follow-up period. The incidence of a negative nutritional outcome will be defined in two different ways according to the baseline nutritional status:

- for children with no malnourishment at time of entry into study, “negative nutritional outcome” is defined as progression to moderate or severe malnourishment,
- for children with moderate malnourishment at time of entry into study, “negative nutritional outcome” is defined as loss of  $\geq 10\%$  of baseline weight or progression to severe malnourishment, whichever is reached first.

Thus, the event of a child reaching a “negative nutritional outcome” at least once within 6 months of follow-up period will be compared between the three study groups.

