#### 5.4.4 Missing endpoint data

The amount, pattern, timing and distribution of missing data of the primary endpoint will be checked by a person blinded to treatment allocation. A decision based upon the result of this check will be made as to whether and how imputation of missing primary endpoint data will be performed as a sensitivity analysis on the ITT population for the analysis in 5.4.1.

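### No planned analysis of the primary endpoint takes account of death: a child who dies without a recorded negative nutritional outcome adds event-free time, and 4.2 read literally drops every child who dies from the per-protocol set

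*SAP*

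**What the plan says.** **Endpoint.** Under SAP 3.1, NNO for a child not malnourished at entry "is defined as progression to moderate or severe malnourishment". For a child with moderate malnourishment at entry it is a loss of at least 10% of baseline weight or "progression to severe malnourishment, whichever is reached first". Death is in neither definition. It appears in 3.2 as a separate secondary endpoint, "Mortality: overall mortality".

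**Primary analysis.** Under 5.3 the rate "will be computed as the number of events divided by total observed person-time in each treatment group". For the event, "the first time a child reaches a negative nutritional outcome will be used". The analysis is on the "intention to treat population with no imputation of missing data".

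**Missing endpoint data.** Section 5.4.4 leaves to a later blinded decision "whether and how imputation of missing primary endpoint data will be performed as a sensitivity analysis on the ITT population". It does not mention death.

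**Per-protocol repeat.** Section 4.2 lists among its exclusions "Patient misses the last scheduled visit (6 months visit"), and also two or more missed visits in a row. No exception is made for a child who has died. Section 5.4.5 repeats the group comparisons on this set.

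**Where deaths would be seen.** Section 5.5 compares the secondary endpoints, mortality included, between arms with explorative p-values. Section 5.6 tabulates serious adverse events by arm, and 5.1 presents the reasons for loss and withdrawal.

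**The concern.** The children enter with malaria, diarrhoea or LRTI, and some are already moderately malnourished. Death and wasting may well share causes in such children, and a child can deteriorate and die between two measurements. Under 5.3 that child's follow-up simply ends. Events over observed person-time then treats the child as if its later NNO risk had been that of the children who lived.

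The RUTF-control rate ratio is at stake. If one arm has more deaths, and those deaths pre-empt NNOs, that arm loses events from its numerator and looks better on the primary endpoint.

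The per-protocol repeat is no independent check. On the literal reading it analyses only children who survived to the 6-month visit. A child who reached NNO and later died is also excluded, so a valid primary event is lost.

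**Working it through.** The SAP states no sample size, NNO rate or mortality, so there is no figure of its own to reproduce. The rules can be traced in the text, and their effect illustrated under stated assumptions.

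**Tracing one child who dies before 6 months**

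- No NNO before death, ITT (5.3): 0 events, and person-time up to death only.
- No NNO before death, per protocol (4.2): excluded, so event-free time is removed.
- NNO before death, ITT: 1 event, counted at the NNO.
- NNO before death, per protocol: excluded, so the event is removed.

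**Assumptions (none from the SAP):** 500 children per arm; 6-month NNO risk of 10%, 20% or 30%; 5, 10 or 15 excess deaths (1% to 3%) in one arm and none in the other; NNO and death both at 0.25 years; 0.5 years of follow-up otherwise. The 6-month follow-up itself is from SAP section 2.

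**Formula:** rate = first NNOs / person-years; ratio = rate in the arm with excess deaths / rate in the other arm.

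**Reference arm, 20% risk:** 100 NNOs; person-years = 100×0.25 + 400×0.5 = 225; rate = 100/225 = 0.444.

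**Case (a): 10 children die who would have reached NNO**

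- NNOs = 90; person-years = 90×0.25 + 10×0.25 + 400×0.5 = 225; rate = 0.400.
- NNO-only ratio = 0.400/0.444 = **0.90**.
- NNO or death: (90 + 10)/225 = 0.444; ratio = **1.00**.
- Per protocol without these 10: 90/(225 − 2.5) = 0.404; ratio = 0.91.
- With the same 10 deaths in both arms, the NNO-only ratio is (90/225)/(90/225) = 1.00. An imbalance in deaths is needed.

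**Case (b): 10 children die who would not have reached NNO**

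- NNOs = 100; person-years = 100×0.25 + 10×0.25 + 390×0.5 = 222.5; rate = 0.449; NNO-only ratio = **1.01**.
- NNO or death: 110/222.5 = 0.494; ratio = **1.11**.

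Ratios for 5, 10 and 15 excess deaths:

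| NNO risk | (a) NNO only | (a) NNO or death | (b) NNO only | (b) NNO or death |
|---|---|---|---|---|
| 10% | 0.90, 0.80, 0.70 | 1.00 | 1.01, 1.01, 1.02 | 1.11, 1.21, 1.32 |
| 20% | 0.95, 0.90, 0.85 | 1.00 | 1.01, 1.01, 1.02 | 1.06, 1.11, 1.17 |
| 30% | 0.97, 0.93, 0.90 | 1.00 | 1.01, 1.01, 1.02 | 1.04, 1.08, 1.12 |

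**Recorded NNO, then death (10 children, 20% risk).** ITT rate = 100/225 = 0.444. Per-protocol rate = 90/(90×0.25 + 400×0.5) = 90/222.5 = 0.404. The per-protocol rate is 0.91 of the ITT rate in that arm (0.81 at 10% risk, 0.94 at 30%).

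**The case against.** The strongest defence is that 5.3 specifies an ordinary event-specific rate. The stated objective is the incidence of acute malnutrition, the endpoint matches it, and time counts only until death. This stands as far as it goes: nothing in 5.3 is miscalculated, and there is no case for replacing the primary endpoint. It does not make the rate ratio interpretable when deaths are unequal and linked to nutrition.

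Four stronger readings are tempting, and the SAP does not support them.

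- *Unequal deaths always bias the ratio.* They do so only if the children who die had a higher NNO risk than survivors. In case (b) the NNO-only ratio stays at 1.01 to 1.02. The link is plausible in this population, but the SAP does not establish it.
- *A difference in deaths would go unseen.* It would not. Mortality is compared by arm, serious adverse events are tabulated by arm, and reasons for loss are presented. What is missing is any planned analysis of the primary endpoint that shows the effect on the rate ratio.
- *Dropping a child who died without NNO from the per-protocol set flatters that arm further.* It does the reverse, slightly: event-free time goes, and the ratio in case (a) moves from 0.90 to 0.91. The real harm of the rule is the loss of recorded NNOs.
- *The gap between an NNO-only ratio and an NNO-or-death ratio measures the bias.* In general it compares two endpoints. In case (b) the gap is 1.01 against 1.11 with essentially no bias. Only in case (a), where the arms are identical by construction, is the gap the bias.

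It is also fair to say that 4.2 does not name death. Whether a child who has died misses a visit is a matter of reading, and the per-protocol analysis is secondary. That is a reason to settle the wording, not to leave it open.

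**Conclusion.** The point holds in conditional form. No planned analysis of the primary endpoint counts death or has a rule for it. If children who die were at higher NNO risk than survivors and deaths differ between arms, the ITT rate ratio is biased in favour of the arm with more deaths. Otherwise it is about unbiased but does not reflect those deaths. On the literal reading of 4.2, the per-protocol analysis conditions on survival to 6 months and discards NNOs already recorded in children who later die.

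The size cannot be taken from the SAP. Under the assumptions above, 1% to 3% excess deaths that all pre-empt an NNO shift a true ratio of 1.00 to between 0.97 and 0.70, furthest when NNO is rare. That is the extreme case, since every excess death is taken to pre-empt an NNO. This does not invalidate the primary analysis, but it is a gap worth closing before deaths by arm are known.

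**What to change.** Keep the primary endpoint and the analysis in 5.3, and make three additions.

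1. In 5.4, add a sensitivity analysis on the ITT population with the same Poisson model. The event is the first of NNO or death, and person-time stops at that event.
2. Report the number of deaths without prior NNO in each arm, beside the primary result.
3. In 4.2, state that scheduled visits falling after death do not count as missed for per-protocol exclusion.

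The cost is one further model run, one line in a results table and a few sentences in the SAP, with no new data beyond the deaths already needed for the mortality endpoint. The drawback is that the composite also counts deaths unrelated to nutrition, so it should remain a sensitivity analysis.
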